#### Patient record data

Data on pregnancy and delivery is comprised of gestational weight gain, postpartum weight retention, blood pressure, pregnancy complications, birth outcomes, newborn data such as birthweight and LGA. In addition, data is collected about several other maternal items: chronic diseases, psychological history, use of medications, diagnoses and complications in previous pregnancies (such as, GDM, preeclampsia, preterm delivery (<37 weeks of gestation) and miscarriage).

#### Well-being data

*Data on dietary intake* that is collected with the mobile app (FatSecret), and the nutritional intake (Calories, Protein, Fat and Carbohydrate) are both included in analysis. The app also displays the data by meal and snack eaten to observe meal patterns. FatSecret has been shown to be accurate and practical [52]. The outcome variable of interest in this study is the total kilocalories per day.

*Data on activity*, *sleep and stress* is collected with the Oura-ring. Studies in the literature have indicated the reliability of the ring in terms of sleep, physical activity, heart rate, and heart rate activity [53–55].

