#### Target group 1: Overweight women

Overweight women (n = 54) were recruited at their first antenatal visit using convenience sampling. The power analysis was calculated based on two scales, self-efficacy in eating (WEL) and physical activity (PASE). Calculations were done with one sided t-tests with an effect size of 0.50, a power level of 0.80 and a significance level of 0.05. A 20% loss was included in the calculation. Based on both scales, a sample of 54 overweight pregnant women was needed to detect the difference in changes in eating self-efficacy or self-efficacy in physical activity.

Women were eligible for inclusion if they were 1) pregnant ≤15 weeks of gestation, 2) ≥18 years of age and 3) overweight or obese (BMI ≥ 25kg/m2) and 4) had adequate language skills in Finnish. Women were excluded if they 1) did not have a mobile device to download applications and synchronize data, 2) had a diagnosis of severe mental illness, 3) were diagnosed diabetes type 1 before pregnancy and/or 4) had mobility limitations.

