**Fig 2 pone.0279696.g002:**
[figure not shown]
The development process of the weight management intervention for overweight pregnant women.

**Step 1**: Development of proposal/targets for improvement were conducted based on previous literature of weight management interventions, national guidelines and local patient record data. Data on pregnancy and delivery, BMI before pregnancy and after delivery, breastfeeding information and depression scores were obtained from the electronic patient records collected in 2018 at one maternity clinic. In order to establish a detailed understanding of the weight management problem, these acquired statistics for the region’s overweight women and the information on obesity and weight management interventions based on the literature [9, 26, 27] were introduced to PHNs (n = 8) and their Nursing Director. A total of 84 pregnant women attended pre-pregnancy care in maternity clinics in 2018 in the area of the two municipalities and the majority (67.9%) were overweight or obese.

**Step 2**: The analysis of performance, the target group and settings were examined through individual interviews with overweight women (n = 11) and focus group interviews with PHNs (n = 5) [28]. Weight management behaviors were identified from the perspective of the maternity care professionals and the overweight and obese women with the help of the Behaviour Change Wheel (BCW) [29]. The results revealed that interventions should offer clear advice and non-judgmental support during pregnancy and after delivery by targeting women’s capabilities, opportunities, and motivation. In addition, health technology could be a valuable component of the intervention, as well as an implementation strategy that would provide ways to approach this topic and support women in maternity clinics. To assess the usability of health technology and wearable devices as a potential intervention element, a purposive sample of overweight and obese women (n = 7) and PHNs (n = 6) wore smart wearables for seven consecutive days. Participants completed a semi-structured diary each day to assess the comfort and usability of the devices and the application. Participants preferred the Oura Smart Ring to the Samsung smart watch, as it was comfortable to wear and had a beautiful appearance.

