#### Secondary outcome

**Weight gain** is measured by PHNs at every antenatal appointment, on average eight times. The women’s weight before delivery is then compared to the national recommendations based on their BMI before pregnancy. For those women whose pre-pregnancy BMI is 25–29.9, the recommended weight gain during pregnancy is 7–11 kg and for those women whose pre-pregnancy BMI is 30 or more, a gain 5–9 kg weight during pregnancy is recommended [38].

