#### Data analysis

The data will be analyzed statistically. Appropriate descriptive statistics will be calculated for the background variables, WEL, PASE, weight change, EPDS, WHOQOL-BREF, PRAQ-R2, PSS-4, SOC-13, TFEQ-R18, 6-FQ, calories consumed, and the Ouras parameters. Variables like the EPDS, baseline BMI and Ouras wear time will be tested for their association with changes in self-efficacy in eating and physical activity. Mixed effect models will be used to evaluate change over time in self-efficacy in eating and physical activity and weight change. Simple mediation models will be used to assess calories consumed and MVPA as mediators between self-efficacy and weight change.

Machine learning and event mining approaches are being exploited in the intervention to build personal models–such as sleep and physical activity–for each individual. The relationships between the collected parameters, including weight gain, physical activity, sleep, and stress will also be investigated. Signal processing and (for example, unsupervised and semi-supervised) machine learning techniques are being exploited to extract events–i.e., high abstraction level information–from the data collected via the Oura ring and the questionnaires. These events characterize pregnant women’s daily life or lifestyle: e.g., their physical activity during the day or stress levels during sleep and these events are defined based on different attributes in certain epochs varying from minutes to a day. The events will be divided into three categories: activity, health, and context. Subsequently, the relationships between the events and their attitudes will be investigated via statistical analysis techniques. For example, when an undesired event (e.g., stress) is detected during pregnancy, statistical analysis techniques (e.g., Chi-Square test) will be used to evaluate the relationships between the event and the mother’s activity, health, and context. Moreover, higher data abstraction will be performed to record events in a chronological order. Data analytic techniques ranging from simple rule-based algorithms to machine learning classifications will be developed to extract patterns from the collected data and events. To this end, machine-learning-based methods (e.g., autoencoders) will be developed to build personalized models, by which the pregnant woman’s real state is compared with the desired state.

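### Total kcal/day is named as the calorie mediator with no adjustment for body size; used as a level, it may distort the calorie-to-weight path, most likely by weakening it

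*Protocol article*

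**What the plan says.** Under Well-being data, the protocol article lists calories, protein, fat and carbohydrate from the food diary and then selects one of them: "The outcome variable of interest in this study is the total kilocalories per day". Under Data analysis it states: "Simple mediation models will be used to assess calories consumed and MVPA as mediators between self-efficacy and weight change". Neither section says whether calories enter as a level or a change, which diaries are used, or which covariates enter.

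Baseline BMI does appear under Data analysis, but for another purpose: "Variables like the EPDS, baseline BMI and Ouras wear time will be tested for their association with changes in self-efficacy". It is collected with the background questionnaire.

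Eligibility (Target group 1) requires a BMI of at least 25 and sets no upper limit. The Secondary outcome section gives recommended gains that differ by class: "For those women whose pre-pregnancy BMI is 25–29.9, the recommended weight gain during pregnancy is 7–11 kg", and for women whose "pre-pregnancy BMI is 30 or more, a gain 5–9 kg weight during pregnancy is recommended". Under SLIM intervention, one-week food diaries are scheduled at gestational week 15 or less, at week 34 and eight weeks after delivery.

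**The concern.** Weight change depends on intake relative to need, and need rises with body size. The second premise is physiological and is not stated in the article. Two women eating the same kcal/day can therefore have different surpluses, and a heavier woman can eat more without any surplus. In a sample with an open-ended BMI range this has two effects on a model that uses kcal levels:

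- **Dilution.** Variation in kcal/day that only tracks body size carries no information about surplus, so it flattens the slope of weight change on calories.
- **Mediator–outcome confounding.** If gain also differs by body size, body size is a common cause of mediator and outcome. It adds a further bias whose sign follows the sign of that difference.

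The mediation model is the plan's test of whether self-efficacy works on weight through eating. The indirect effect is the product of the self-efficacy-to-calories path and the calories-to-weight path, so a weakened second path shrinks the indirect effect in proportion. The trial could then report that calories play little part when the measure was at fault. Feedback and goal setting in this intervention draw on the same diary.

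**Working it through.** The article gives no mediation effect, no SD of kcal/day and no SD of weight gain, so there is no stated figure to reproduce. The size has to be explored under assumptions.

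**Model.** Let kcal = 800 + k × weight + surplus, and gain = 9 + b × surplus + g × (BMI ≥ 30) + noise with SD 4 kg. The midpoint of 7–11 kg is 9 and that of 5–9 kg is 7, so g = −2 kg corresponds to actual gain following the recommendations exactly. Self-efficacy is left out, taken as independent of body size.

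**Formula.** With surplus independent of body size, the unadjusted slope of gain on kcal is

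slope = [b × Var(surplus) + g × k × Cov(weight, BMI ≥ 30)] / [Var(surplus) + k² × Var(weight)].

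**Main range.** Assumed: k = 10 to 20 kcal/day per kg, SD of surplus 300 to 500 kcal/day, SD of weight about 13 kg, b = 0.003 to 0.01 kg per kcal/day. With g = 0 the ratio of estimated to true slope is Var(surplus) / [Var(surplus) + k² × Var(weight)]:

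- Mildest case: 500² / (500² + (10 × 13)²) = 250,000 / 266,900 = 0.94.
- Strongest case: 300² / (300² + (20 × 13)²) = 90,000 / 157,600 = 0.57. Simulation of 400,000 women gives 0.55, since the weight SD is only approximately 13 kg.

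Simulated ratios over the whole grid:

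| Model | Ratio to true slope |
|---|---|
| kcal level, unadjusted, g = 0 | 0.55–0.94 |
| kcal level, unadjusted, g = −2 kg | 0.19–0.90 |
| kcal level, unadjusted, g = +2 kg | 0.67–1.12 |
| kcal level, linear baseline BMI added | 0.85–0.99 |
| kcal level, weight and BMI class added | about 1.00 |
| within-woman change in kcal, g = −2 kg | about 1.00 |

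No sign change occurred anywhere on this grid.

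**Can the sign change?** Take a smaller spread of surplus: SD 200 kcal/day, k = 15, height 1.65 m, BMI with mean 30 and SD 3.5.

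- SD of weight = 3.5 × 1.65² = 9.53 kg, and k × SD = 142.9 kcal/day.
- Denominator = 200² + 142.9² = 40,000 + 20,420 = 60,420.
- k × Cov(weight, BMI ≥ 30) = 142.9 × 0.399 = 57.0, where 0.399 is the standard normal density at zero.
- With g = −2 kg, the added term is −114 / 60,420 = −0.19 kg per 100 kcal/day.
- The dilution factor is 40,000 / 60,420 = 0.66.

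True slopes of 0.2, 0.5 and 1.0 kg per 100 kcal/day therefore become 0.13 − 0.19 = −0.06, 0.33 − 0.19 = 0.14 and 0.66 − 0.19 = 0.47. Simulation agrees. Only the smallest slope changes sign. Changing one assumption at a time:

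| Gap g, SD of surplus | Estimates for true 0.2 / 0.5 / 1.0 |
|---|---|
| −2 kg, 200 | −0.06 / 0.14 / 0.47 |
| −2 kg, 200, BMI cut off at 25 | −0.04 / 0.19 / 0.54 |
| −2 kg, 300 | 0.06 / 0.31 / 0.71 |
| −1 kg, 200 | 0.04 / 0.23 / 0.57 |
| none, 200 | 0.13 / 0.33 / 0.66 |
| +2 kg, 200 | 0.32 / 0.52 / 0.85 |

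With BMI and BMI class in the model, the first scenario returns 0.20, 0.50 and 1.00. Height is fixed there, so BMI carries all of body weight.

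**The case against.** The strongest reply is that the article gives mediation one sentence. Simple mediation ordinarily means a single mediator and does not rule out covariates. Naming kcal/day selects it from four nutrients without excluding adjustment. Covariates and coding are commonly left to a statistical analysis plan, which is not shown, and the three diaries would allow a change score. This stands as far as it goes: silence is not a decision to omit adjustment, so the point is conditional on kcal levels being used as written. It does not dispose of the point, because the article does fix the measure in absolute terms and names baseline BMI only for a different analysis.

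A reader might go further and infer that the calorie path is certain to be biased toward zero, or reversed. The documents do not support that. The 2 kg difference is between recommended gains, not observed ones, and the Discussion says half of overweight or obese women gain more than the guideline it cites. If heavier women gain more, the bias can run upward. A change of sign needs the full 2 kg gap, a surplus SD near 200 kcal/day and a small true slope together.

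A reader might also infer that breastfeeding distorts the calorie path through the postpartum diary. That is speculative. The article does not say that this diary enters the mediation, and the secondary outcome is gain during pregnancy. Breastfeeding is not named under Patient record data, but that list may be condensed. The development step does show that local records held it in 2018 ("BMI before pregnancy and after delivery, breastfeeding information and depression scores were obtained from the electronic patient records").

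**Conclusion.** The point holds in conditional form. A simple mediation model on kcal/day levels, without a body-size term, leaves body size uncontrolled in the calorie-to-weight path. Attenuation is the most likely result, and it deepens if heavier women gain less, but neither its direction nor its size is settled by the article. The figures rest on assumed values for energy need per kg, spread of surplus, spread of weight and true slope. They also take self-efficacy as independent of body size and ignore diary error. This is a minor weakness confined to the mechanism analysis. The self-efficacy outcomes (WEL and PASE) and the models of change over time are untouched.

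**What to change.** Add one sentence under Data analysis that does one of the following:

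- include baseline weight (or pre-pregnancy BMI) and BMI class as covariates in the calorie mediation model; or
- use each woman's change in kcal/day between diaries as the mediator, and say which diaries.

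Weight with BMI class removed the bias in the simulations. Linear BMI alone left 0.85 to 0.99 of the slope. The change score also removed it, but it asks a slightly different question (change in intake rather than its level), so the choice should be stated in advance. Either way, say whether the eight-week postpartum diary is used.

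Expressing intake relative to estimated energy requirement is another option, but it needs an outside prediction equation with its own error and is not necessary here.

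BMI is already collected and the diaries are already scheduled, so no new data are needed. The covariate option costs one or two more model terms with 54 women, or about 43 after the planned 20% loss (54 × 0.8 = 43.2).

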#### Data analysis

The data will be analyzed statistically. Appropriate descriptive statistics will be calculated for the background variables, WEL, PASE, weight change, EPDS, WHOQOL-BREF, PRAQ-R2, PSS-4, SOC-13, TFEQ-R18, 6-FQ, calories consumed, and the Ouras parameters. Variables like the EPDS, baseline BMI and Ouras wear time will be tested for their association with changes in self-efficacy in eating and physical activity. Mixed effect models will be used to evaluate change over time in self-efficacy in eating and physical activity and weight change. Simple mediation models will be used to assess calories consumed and MVPA as mediators between self-efficacy and weight change.

Machine learning and event mining approaches are being exploited in the intervention to build personal models–such as sleep and physical activity–for each individual. The relationships between the collected parameters, including weight gain, physical activity, sleep, and stress will also be investigated. Signal processing and (for example, unsupervised and semi-supervised) machine learning techniques are being exploited to extract events–i.e., high abstraction level information–from the data collected via the Oura ring and the questionnaires. These events characterize pregnant women’s daily life or lifestyle: e.g., their physical activity during the day or stress levels during sleep and these events are defined based on different attributes in certain epochs varying from minutes to a day. The events will be divided into three categories: activity, health, and context. Subsequently, the relationships between the events and their attitudes will be investigated via statistical analysis techniques. For example, when an undesired event (e.g., stress) is detected during pregnancy, statistical analysis techniques (e.g., Chi-Square test) will be used to evaluate the relationships between the event and the mother’s activity, health, and context. Moreover, higher data abstraction will be performed to record events in a chronological order. Data analytic techniques ranging from simple rule-based algorithms to machine learning classifications will be developed to extract patterns from the collected data and events. To this end, machine-learning-based methods (e.g., autoencoders) will be developed to build personalized models, by which the pregnant woman’s real state is compared with the desired state.

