### SLIM intervention

The core components of the SLIM intervention are *health technology*, *motivational interviewing*, *feedback and goal setting*. Health technology includes the Oura-ring, an electronic food diary and a SLIM application. The Oura ring is a commercial wearable ring that captures various health parameters and provides various daily scores for the user. The ring–equipped with different biosensors including a built-in photoplethysmography (PPG) sensor and an inertial measurement unit (IMU)–provides heart rate, nocturnal heart rate variability, nocturnal respiration rate, sleep duration, body temperature, and step counts. The ring is water resistant, lightweight and easy to use for short-term and long-term monitoring. The ring’s battery allows up to one-week data collection per charge. The collected data are transferred to the Oura mobile app (iOS or Android) via Bluetooth and then to the cloud server [31]. Participants wear the Oura rings continuously starting from gestational week 15 or less and continue until the postnatal visit 12 weeks after delivery. The electronic food diary, FatSecret is a free of charge, online diet, nutrition and weight loss service that allows users to set up unique user profiles, track their activity, food intake and weight. The services offered by FatSecret include the FatSecret websites and mobile applications [32]. Participants complete a food diary for one week at three timepoints: gestational week 15 or less, gestational week 34 and eight weeks after the delivery. The SLIM application is a platform that enables researchers to send e.g. questionnaires and surveys to participants. PHNs utilize the data monitored and collected with the Oura smart ring and the food diary during routine maternity care visits to evaluate physical activity, sleep and nutrition. PHNs give feedback to the women based on the data. They use motivational interviewing focusing on helping individuals to identify and resolve any ambivalence about changing behavior [33], and create goals in collaboration with women. The goals are documented in patient records. Participants are asked to answer questionnaires at three timepoints: gestational week 15 or less, gestational week 34 and 12 weeks after the delivery.

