#### Outcome measures

The primary outcomes for the effectiveness of the intervention are self-efficacy in eating and physical activity and reduced weight gain during pregnancy (secondary outcome). To track variations and trends, health parameters are collected, these include: weight retention postpartum, depressive symptoms, quality of life, pregnancy specific anxiety, perceived stress, sense of coherence, eating behavior and lifestyle patterns, physical activity levels, sleep quality, stress levels and dietary intake. (Fig 1).

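### The one test named for relating detected events, a chi-square test, ignores gestational week and repeated records, so shared drift over pregnancy can appear as a relationship

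*Protocol article*

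**What the plan says.** All statements are from the protocol article.

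- **Data analysis**, on parameters in general: "The relationships between the collected parameters, including weight gain, physical activity, sleep, and stress will also be investigated". No method is attached to this sentence.
- **Data analysis**, on an undesired event detected during pregnancy: "statistical analysis techniques (e.g., Chi-Square test) will be used to evaluate the relationships between the event and the" woman's activity, health and context. The chi-square test is introduced as an example, and no other association test is named for events.
- **Data analysis**, on the unit of record: "these events are defined based on different attributes in certain epochs varying from minutes to a day". Each woman therefore contributes many records.
- **SLIM intervention**, on the observation period: "Participants wear the Oura rings continuously starting from gestational week 15 or less and continue until the postnatal visit 12 weeks after delivery".
- **Secondary outcome**: weight is "measured by PHNs at every antenatal appointment, on average eight times", and the recommended gains are 7-11 kg (BMI 25-29.9) and 5-9 kg (BMI 30 or more).
- **Outcome measures**: "To track variations and trends, health parameters are collected". The authors therefore look for change over time, but give no size or direction for it in the ring signals.

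Mixed effect models are assigned to change over time in self-efficacy and in weight. They are not mentioned for the event relationships. Events are to be put in chronological order, but the article does not describe this as an adjustment of any test.

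**The concern.** A chi-square test on a table of event by activity pools all days and treats each record as independent. If both the event and the activity category become more common (or one more and the other less common) as pregnancy advances, late-pregnancy records fall together in one corner of the table. The test then shows an association even where, within any given week, the two are unrelated.

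Accounting for the woman alone does not remove this, because the drift takes place within each woman. It is therefore a separate matter from clustering, although the named test ignores both.

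What is at stake is the part of the first aim that extracts events and patterns from the health data. Advancing pregnancy could be reported as, say, stress going with inactivity. The same applies to relating weight gain to activity, sleep or stress, since weight is the one listed parameter whose rise in pregnancy is evident from the article itself.

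**Working it through.** The article states no figure for these analyses, so there is none to reproduce. The question is how far shared drift moves the error rate of the named test.

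**Inputs**
- Women: 54 with 20% loss (Target group 1), so 54 × 0.80 = 43.2, taken as 43.
- Period: 25 weeks of pregnancy, 25 × 7 = 175 days. This is an assumption. It is kept to pregnancy because the chi-square example is.
- Record: one per woman per day, within the stated range of epochs. N = 43 × 175 = 7,525.
- Two truly unrelated yes/no events, each at a mean rate of about 20%, with the same drift on the logit scale. Rate and drift are assumptions.
- Spread between women: 0 or 0.5 on the logit scale, drawn independently for the two events (assumption).
- Two-sided 0.05, 500 runs per scenario. The Monte Carlo standard error near 5% is √(0.05 × 0.95 / 500) ≈ 0.01.

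**Approximation by formula.** If both rates move roughly linearly from a to b, the pooled table acquires covariance (b − a)²/12. With mean rate p = (a + b)/2, the correlation is φ = [(b − a)²/12] / [p(1 − p)]. The test statistic is centred at z = φ√N, and the rejection rate is Φ(z − 1.96) + Φ(−z − 1.96).

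- 16% to 24%: 0.08²/12 = 0.00053; φ = 0.00053/0.16 = 0.0033; z = 0.0033 × 86.7 = 0.29; rejection 0.06.
- 13% to 29%: 0.16²/12 = 0.00213; φ = 0.00213/0.166 = 0.0129; z = 1.12; rejection 0.20.
- 11% to 35%: 0.24²/12 = 0.0048; φ = 0.0048/0.177 = 0.027; z = 2.35; rejection 0.65.
- 8% to 40%: 0.32²/12 = 0.00853; φ = 0.00853/0.182 = 0.047; z = 4.06; rejection 0.98.

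**Simulation** (false-positive rate, between-woman SD 0 / 0.5)

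| Event rate, start to end | Formula | Pooled chi-square | One woman's 175 days | Strata of woman × week |
|---|---|---|---|---|
| 20% to 20% | 0.05 | 0.06 / 0.07 | 0.06 / 0.03 | 0.05 / 0.05 |
| 18% to 22% | 0.05 | 0.06 / 0.07 | 0.04 / 0.04 | 0.06 / 0.06 |
| 16% to 24% | 0.06 | 0.06 / 0.08 | 0.06 / 0.05 | 0.06 / 0.05 |
| 13% to 29% | 0.20 | 0.19 / 0.24 | 0.03 / 0.06 | 0.05 / 0.06 |
| 11% to 35% | 0.65 | 0.70 / 0.67 | 0.06 / 0.08 | 0.07 / 0.04 |
| 8% to 40% | 0.98 | 1.00 / 0.98 | 0.13 / 0.13 | 0.04 / 0.04 |

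The last column is a Cochran-Mantel-Haenszel test. Stratified by week only, the rate is 0.05-0.07 at SD 0 and 0.06-0.11 at SD 0.5, so the woman belongs in the strata too.

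**Reading**
- Formula and simulation agree. The spurious correlation is small (φ up to about 0.05). It becomes significant because there are thousands of records.
- When every woman drifts alike, the covariance within each woman is the same as in the pooled table. Strata by woman alone would leave z almost unchanged.
- Both signals must drift. If only one does, the covariance is zero.
- Day-to-day autocorrelation, and woman-level tendencies shared by the two events, were not simulated.

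**The case against.** The strongest reply is that this treats an illustration as the plan. The general sentence on relationships fixes no method, the chi-square test is only an example, nothing excludes gestational week, and a journal article may leave such detail to a fuller plan. That stands against any claim that the authors have committed to an unadjusted analysis. It does not remove the point: the one method offered is unsuited to the repeated, time-ordered records that the same section describes, and a fuller plan written from it would carry the fault over.

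Second, an association that includes gestational change can be a legitimate description, given that the article sets out to track trends. This also stands. The fault arises when such an association is read as a link between event and behaviour.

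A reader might infer more than the article supports:

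- *That unrelated signals will be declared related.* Ring-signal drift is not quantified. With small drift the error stays at 6-8%, and within one woman's data it stays near nominal except at the strongest drift (0.13).
- *That stress events are defined against a woman's early-pregnancy values, so that late pregnancy is labelled stress.* No such baseline is described.
- *That the personalized models rest on the chi-square results.* They are described as built for each individual by machine-learning methods such as autoencoders, with no stated input from these tests.
- *That pregnancy and postpartum records are mixed in this test.* The example concerns events detected during pregnancy.

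**Conclusion.** The point holds in limited form. The only association test named for detected events takes no account of gestational week or of the woman. Where two signals both drift materially over pregnancy, it can declare unrelated events related well above 5%: about 20% of the time when event rates go from 13% to 29%, and 70-100% when they go from 11% to 35% or from 8% to 40%. For drift up to 16% to 24% the rate is 6-8%. Conditioning on woman and week brings it to about 5% throughout.

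These sizes rest on assumed drift, an assumed event rate of about 20%, daily records and 43 women. Other drift or epoch lengths would change them; at the same φ, z grows with the square root of the number of records. The analysis is exploratory, and neither the primary outcomes nor weight gain as secondary outcome is affected.

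**What to change.** In the Data analysis section, replace the chi-square example with an analysis conditional on woman and gestational week. Either of these would serve:

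- a mixed or conditional logistic model for the event, with woman as the cluster or stratum and a smooth term for gestational week; or
- a Mantel-Haenszel analysis in strata of woman by week.

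State that the same adjustment for gestational time applies when weight gain, activity, sleep and stress are related to one another. If the unadjusted association is also wanted as a description, report it beside the adjusted one and say that it includes change due to advancing pregnancy.

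The cost is a change of wording, a little more modelling and some precision: strata in which event or activity does not vary contribute nothing, and the smooth term uses degrees of freedom. No new data should be needed, since gestational week should be derivable for dated records.

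### The chi-square test named for event associations does not fit repeated epochs within women unless there is one record per woman

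*Protocol article*

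**What the plan says.** The Data analysis section of the protocol article describes extracting events from the ring and questionnaire data, and states that "these events are defined based on different attributes in certain epochs varying from minutes to a day". Events are sorted into activity, health and context. The section then illustrates the next step, taking stress in pregnancy as the undesired event. Its wording is "statistical analysis techniques (e.g., Chi-Square test) will be used to evaluate the relationships between the event and the", and it goes on to name the woman's activity, health and context as the other side of the relationship.

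The SLIM intervention section sets the monitoring period: "Participants wear the Oura rings continuously starting from gestational week 15 or less and continue until the postnatal visit 12 weeks after delivery". The section on target group 1 gives the number of independent units, "a sample of 54 overweight pregnant women was needed", and adds "A 20% loss was included in the calculation".

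Repeated measures are handled explicitly elsewhere in the same section: "Mixed effect models will be used to evaluate change over time in self-efficacy in eating and physical activity and weight change". No such step is named for the event associations. The text does not say what a row of the chi-square table is, whether women are pooled, or whether the analysis is done woman by woman.

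**The concern.** A chi-square test of a two-way table is valid when each row of data is an independent observation. The events defined here recur many times in the same woman. Some women will be stressed more often than others and some will be active more often than others. Consecutive days or minutes will also resemble one another. When both the event and the factor behave this way, chance alignment across a few dozen women, or across a few long runs within one woman, looks like association over a large number of records. The test then rejects too often.

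The contrast within the section adds weight. Questionnaires are completed at three time points and weight is measured about eight times, and these sparse series get mixed models. The far denser ring data get a chi-square example. At stake is the credibility of the reported links between stress and activity, health or context, which belong to the first aim.

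**Working it through.** The documents give no error rate, sample size or power figure for the event analysis, so there is no figure of the plan's own to reproduce. The check asks how far the named test can drift from 5% when there is no true association.

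**Inputs from the article.** 54 women; 20% loss, so 54 × 0.8 ≈ 43; epochs up to one day; continuous wear from week 15 or less; example restricted to pregnancy.

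**Assumptions not in the article.** Entry at week 15, delivery at week 40, daily epochs, factor present on 30% of days, event on 20% of days, latent-scale ICC 0 to 0.3, day-to-day autocorrelation 0 to 0.8.

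**Volume.** Pregnancy: (40 − 15) × 7 = 175 days per woman. To 12 weeks after delivery: (25 + 12) × 7 = 259 days. For 54 women this is 54 × 175 = 9,450 to 54 × 259 = 13,986 woman-days. For 43 women it is 7,525 to 11,137. The records run to thousands even at the coarsest epoch.

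**Pooled over women, closed form.** With m days per woman, and within-woman correlations r_X (factor) and r_Y (event) of the binary records, the chi-square statistic is inflated by about

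D = 1 + (m − 1) · r_X · r_Y,

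and the false-positive rate is about 2[1 − Φ(1.96/√D)]. The binary correlation follows from the latent ICC as r = (P₁₁ − p²)/(p(1 − p)), where P₁₁ is the bivariate-normal probability that two days in one woman are both positive. With m = 175:

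| Latent ICC, both variables | r_X | r_Y | D | Closed form | Simulation |
|---|---|---|---|---|---|
| 0.1 | 0.0584 | 0.0507 | 1 + 174 × 0.0584 × 0.0507 = 1.52 | 11% | 12–13% |
| 0.2 | 0.1188 | 0.1051 | 1 + 174 × 0.1188 × 0.1051 = 3.17 | 27% | 26% |
| 0.3 | 0.1816 | 0.1634 | 1 + 174 × 0.1816 × 0.1634 = 6.16 | 43% | 41–47% |

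The simulation column gives the range over separate Monte Carlo runs with 54 women. With 2,000 replicates the standard error near 41% is √(0.41 × 0.59/2000) ≈ 1.1 points. The spread at ICC 0.3 is therefore more than noise and shows that the size depends on how the clustering is generated. Treat it as a rough range.

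The formula also shows when there is no problem: if r_X or r_Y is zero, D = 1. The simulation agrees, with 5.5% when neither variable is clustered and 5.2% when only the event is (ICC 0.2). The number of women does not enter D: with 43 women and ICC 0.2 the rate is 26%. Extending to 259 days at ICC 0.2 raises it to 33%.

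**Within one woman, 175 days, both series autocorrelated.** 5.2% at autocorrelation 0 and at 0.3; 8–10% at 0.5; 21–22% at 0.8.

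**Alternatives, same null data.**
- A test clustered on the woman (robust variance from per-woman score totals) rejects in 4.0% to 5.0% of data sets in every scenario, including those with autocorrelation 0.5.
- A Mantel–Haenszel test stratified by woman rejects in 4.1% to 5.5% without serial correlation, but about 8% with autocorrelation 0.5. Removing differences between women is therefore not enough if days are serially correlated.
- Chi-square with one record per woman (n = 54) rejects in 4.6%.

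**The case against.** The strongest reply is that the article does not commit to the faulty analysis. Chi-square appears as an example inside an example. A reader might infer that thousands of epochs are pooled and treated as independent, but the text never says so, and one record per woman would be valid. This stands. The point can only be conditional.

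It is also fair that inflation is not automatic. A reader might conclude that false associations will follow, but clustering or serial correlation is needed in both variables, and at autocorrelation 0.3 within one woman there is practically none. Against this, activity, health and context are themselves event categories drawn from the same women, so clustering on both sides is the natural expectation, even though its size is unknown.

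A third reply is that a journal article may leave the unit of analysis to a fuller plan. That covers omitted detail. It does not cover naming a test that misfits the data as the same section describes them, on both the pooled and the single-woman reading. The one-record-per-woman reading is valid but discards the epoch structure. With an event on 20% of days, practically every woman would have at least one in 175 days, so an ever/never table would be nearly empty on one side, and a different woman-level summary would be needed.

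Finally, a reader might infer that the personal models rest on these p-values. The documents do not support that: the models are to be built by machine learning such as autoencoders, and nothing says that chi-square results select or feed them.

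**Conclusion.** The concern holds in conditional form. The example test is unsuitable for repeated within-woman epochs, and the article names no adjustment for this step. If applied to epoch records with both variables clustered, its error at nominal 5% would be about 12% at ICC 0.1, 26% at 0.2 and 41% to 47% at 0.3 over 54 women × 175 days. Within one woman it would be about 5% to 22% at autocorrelation 0.3 to 0.8. These sizes rest on assumed ICCs, autocorrelations, prevalences and a week-40 delivery. The 175-day figures are the relevant ones because the example concerns pregnancy.

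The reach is limited. Self-efficacy and weight gain are analysed with mixed models, so a reader should not extend this point to the primary or secondary outcomes. It concerns exploratory event associations only. It is a moderate improvement worth making because it is cheap, and not a must-fix.

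**What to change.** In the Data analysis section, state the unit of analysis for the event associations and replace the chi-square example:

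- For epoch records pooled over women, use a test clustered on the woman: generalised estimating equations with robust errors, or a logistic mixed model. The robust clustered test is the version checked above. A mixed model with only a woman-level intercept should also allow for serial correlation, given the stratified test's 8%.
- For analyses of a single woman, use a method that allows for serial correlation, such as a block permutation test.
- Keep chi-square only for tables with one record per woman.

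The cost is a few lines of text, modest programming on the same data, and less favourable p-values. No data collection changes.
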